## Abstract

**Background:**

Convincing evidence suggests that the risk of colorectal cancer (CRC) is increased by the typical Western diet characterized by high consumption of red and processed meat. In addition, some epidemiological studies suggest a reduction in the risk of CRC associated with fish consumption. The role of the gut microbiome in this diet-associated risk is not well understood.

**Methods/design:**

This is a randomized parallel open clinical trial comprising a total of 150 clinically healthy subjects randomly assigned to three groups: a meat-based diet of which 4 portions per week are red meat (1 portion = 150 g), 3 portions per week are processed meat (1 portion = 50 g), and 1 portion per week is poultry (1 portion = 150 g), for a total amount of 900 g per week of meat and derivatives; a meat-based diet supplemented with alpha-tocopherol; and a pesco-vegetarian diet excluding fresh and processed meat and poultry, but which includes 3 portions per week of fish for a total amount of 450 g per week. Each intervention will last 3 months. The three diets will be isocaloric and of three different sizes according to specific energy requirements. Anthropometric measurements, body composition, and blood and fecal samples will be obtained from each participant at the beginning and end of each intervention phase. The measure of the primary outcome will be the change from baseline in DNA damage induced by fecal water using the comet assay in a cellular model. Secondary outcome measures will be changes in the profile of fecal microbiomes, global fecal and urinary peroxidation markers, and neoplastic biomarkers.

**Discussion:**

Although epidemiological data support the promoting role of meat and the possible protective role of fish in colon carcinogenesis, no study has directly compared dietary profiles characterized by the presence of these two food groups and the role of the gut microbiome in these diet-associated CRC risks. This study will test the effect of these dietary profiles on validated CRC risk biomarkers.

**Trial registration:**

ClinicalTrials.gov, NCT03416777. Registered on 3 May 2018.

## Background

Colorectal cancer (CRC) is the second leading cause of cancer death in Europe. The geographical variation of incidence shows how environmental factors, particularly eating habits, play an important role in this disease [1]. Compelling evidence suggests that the risk of CRC is increased by consumption of red and processed meat as well as decreased by foods containing dietary fiber [2]. Although epidemiological studies suggest a reduction in the risk of CRC associated with fish consumption, the evidence for this link is still limited [2]. For non-starchy vegetables and fruits, although there is evidence indicative of a protective effect, this evidence is similarly considered limited and therefore less convincing than the promoting effect of red and processed meat [3].

Several hypotheses have been proposed to explain the association between red and processed meat and CRC: meat-based diets contain carcinogens formed during cooking but also lipid peroxidation and *N*-nitroso compounds whose formation is catalyzed by heme iron present in the colon following red and processed meat consumption [4]. Recent experimental studies [4, 5], epidemiological studies on the E3N cohort [6], and the randomized, double-blind, placebo-controlled SU.VI.MAX study [7] have demonstrated respectively the central role of heme iron and iron-induced peroxidation. On this basis, it has also been shown that antioxidants, in particular tocopherol, may help prevent colon cancer by decreasing the formation of mutagens arising from the peroxidation of fecal lipids, by decreasing oxidative stress in the epithelial cells of the colon, and by molecular mechanisms that influence cell death, cell cycle, and transcriptional events [6, 7]. Moreover, recent data have shown that consumption of a heme iron-enriched diet results in the alteration of gut microbiota consumption and function in rats that was associated with gut barrier defects, and that the gut microbiota is involved in heme-induced peroxidation [8]. On this basis, it has been reported that this microbiota is necessary for heme-induced hyperplasia and epithelial hyperplasia [9]. Despite these results, the role of the intestinal microbiome in determining the risk of cancer associated with red and processed meat has not yet been clarified.

The microbial fermentation of plant foods, associated with a low risk of CRC, increases intestinal short chain fatty acids (SCFAs), including butyrate, which has antineoplastic activity through its inhibition of histone deacetylase and the promotion of apoptosis [10], and also increases activated microbial phytochemicals, such as polyphenols with anti-inflammatory and antioxidant properties [11]. Consequently, it is known that diet influences the composition of the intestinal microbiome, as described by our group in a study on a rural human population [12], and the emerging evidence implies an involvement of the intestinal microbiota in CRC.

Cohort studies with subjects who consume various types of diets (e.g., omnivores, vegetarians, vegans) suggest that the diet alters the intestinal microbiome and the cytotoxic and genotoxic activities of the luminal colonic content [13]. However, although the association between the intestinal microbiota and the CRC is conceptually interesting, these results do not help to explain the mechanisms underlying the modulation of the intestinal microbiota by diet and the consequent impact on CRC risk.

We aimed to design this randomized, open, parallel clinical trial that will test whether diet effects on CRC risks are mediated by interaction with the intestinal microbiota and whether meat-based and pesco-vegetarian diets differentially modulate CRC risk biomarkers in clinically healthy subjects.

## Methods/design

### Study design

The randomized, open, parallel clinical trial will be conducted at the Unit of Clinical Nutrition of the Careggi University Hospital in Florence, Italy. The study design follows the Standard Protocol Items: Recommendations for Interventional Trials (SPIRIT) guidelines (see Fig. 1 and Additional file 1).

**Fig. 1 Fig1:**
[figure not shown]
Time schedule of enrollment, interventions, and assessments for participants

### Eligibility criteria

Clinically healthy subjects (both sexes), aged 18–50 years, will be included in the study. The study population will be selected between these particular ages because after 50 years the risk of CRC shows a significant increase in incidence.

*Exclusion criteria* are the presence of current illness or unstable conditions that need medical supervision, current or recent (past 2 months) use of antibiotics or probiotics, pregnancy or intention to become pregnant in the next 12 months, lactation, smoking habit, and current or recent (past 2 months) adoption of vegetarian or vegan diets.

### Interventions and participant timeline

This clinical randomized study will use a parallel design with three intervention periods. After a 2-week run-in period, the eligible participants will be randomly assigned to three diets differing in the associated CRC risk: a meat-based diet (MBD, high risk), a nutritional control of a high-risk diet (MBD with alpha-tocopherol, MBD-T, presumably medium risk), and a pesco-vegetarian diet (PVD, low risk). Each diet period will last 3 months. The MBD will include 4 portions per week of red meat (1 portion = 150 g), 3 portions per week of processed meat (1 portion = 50 g), and 1 portion per week of poultry (1 portion = 150 g), for a total amount of 900 g per week of meat. The MBD-T with a nutritionally controlled risk will be similar to the MBD but supplemented with 100 mg/day of alpha-tocopherol. The PVD will exclude fresh and processed meat and poultry but will include 3 portions per week of fish, excluding shellfish (1 portion = 150 g), for a total amount of 450 g per week. The diets will contain other sources of proteins (e.g., eggs, dairy, legumes/beans), will be isocaloric, and will derive about 30% of energy from fats, 15% to 20% from proteins, and the rest from carbohydrates (mainly complex). No meals or supplements will be provided. Participants will prepare their meals or eat at restaurants. For all the diets, alcoholic beverages will be limited to one per day for women and two per day for men. Participants will be asked not to alter their physical exercise habits during the study.

The standardized baseline assessment for the intervention and control groups will include a questionnaire regarding demographic information, risk factors, and comorbidity. Furthermore, at the baseline visit, participants will be instructed on the objectives and methods of the clinical trial. Subjects who agree to participate in the study, after signing the informed consent, will be included and randomly divided into three groups, each assigned to consume the MBD, MBD-T, or PVD. Each participant will have to complete a 3-day dietary record (for 2 weekdays and a weekend day) before starting, and a dietician will analyze all 3-day dietary records using a country-specific food-nutrient database.

The study procedures are depicted in Fig. 2. There will be two clinical evaluations of the study population: at the beginning (Time 0) and at the end of the dietary interventions (Time 1).

**Fig. 2 Fig2:**
[figure not shown]
Organization of the intervention study

### Outcome measures

#### Primary outcome

The primary outcome will be DNA damage (strand breaks and oxidized bases) in a human colon cancer cell line (HT29) exposed to fecal water. Genotoxic activity of fecal water will be determined by the comet assay, which evaluates the induction of DNA strand breaks and oxidized DNA bases upon exposure of the cells to fecal water [14]. The metric used will be changes in means from Time 0 to Time 1. Image acquisition will be performed with the Comet Assay IV software (Perceptive Instruments, UK). For each fecal water sample there will be a genotoxicity index (a single figure representing the mean area of the Comet tail [the percentage of DNA in the tail] measured in 100 cells). This figure will then be used in multivariate analyses to predict the potential operational taxonomy units (OTUs) measured using metagenomics approaches, potentially providing specific metabolic functions associated with the risk of neoplastic transformation [15, 16]. For this reason, this outcome was selected as the primary outcome of the study. In a previous study [14], fecal water activity markers were affected by specific dietary components linked with CRC risk such as red meat, and were sensitive to dietary supplementation with chemopreventive agents.

#### Secondary outcomes

Secondary outcomes will be measured in stool samples, blood, and urine. The metric used will be changes in means from Time 0 to Time 1. Regarding stool samples, we will evaluate the following:
Fecal microbiota profile (fungi and bacteria) and fecal targeted metabolomic profile (SCFAs, amino acids, and secondary bile acids) changes from baseline. Total microbial DNA will be extracted from the participants’ faces using repeated bead-beating. The V3 and V4 hypervariable regions of the 16S rRNA gene for bacteria and the internal transcribed spacer (ITS1–4) for fungi will be sequenced on an Illumina MiSeq platform, following the Illumina protocol for 16S Metagenomic Sequencing Library Preparation. SCFAs, amino acids, and secondary bile acids will be measured by mass spectrometry (MS) on fecal samples. SCFAs will be analyzed using gas chromatography (GC)-MS, and bile acids by high-performance liquid chromatography (HPLC)–MS/MS analysis based on retention times and accurate masses of metabolites. The metabolites will be targeted and will be reported in absolute concentration. The amino acids will be analyzed by a combination of ultra high-performance liquid chromatography (UHPLC)-based hydrophilic interaction liquid chromatography (HILIC) and hybrid quadrupole time-of-flight (Q-Tof™) MS. The outcome measure will permit us to describe if and how the microbiome and the relative metabolomic profiles in clinically healthy subjects consuming three diets differing in their content of meat, meat products, and fish will change from baseline level. Numerous pathogenic microbes are known to promote CRC, but there is still limited evidence describing the impact of the diet on the composition of the fecal microbial populations and relative metabolites [17].Fecal water untargeted metabolomic profile changes from baseline. On selected samples, based on fecal water genotoxicity results, we will perform untargeted metabolomics by using one-dimensional (1H) nuclear magnetic resonance (NMR) spectroscopy. The outcome measure will permit us to analyze the qualitative change of fecal waters (bioavailable parts of fecal material) and potentially to identify new biomarkers associated with CRC risk.Mutagenicity and toxicity of fecal water changes from baseline [13, 14, 18]. The mutagenicity of fecal water will be tested using yeast as a model. The test will be performed in exponentially growing cells, because in these conditions cells are metabolically active. After the treatment, cell suspensions will be plated on complete media to detect viability and on two different selective media (without ilv or without trp) plates to evaluate survival and genetic effect.Markers of global peroxidation of fecal water (thiobarbituric acid reactive substances [TBARs]) and specific peroxidation of omega-3 and omega-6 polyunsaturated fatty acids (PUFAs) in fecal water changes from baseline [18, 19]. The level of global and specific peroxidation will be explored with the assay of respectively free 4-hydroxy hexenal (4-HHE) and free 4-hydroxy-2-nonenal (4-HNE). After derivatization, HHE and HNE determinations in fecal waters will be achieved by a sensitive and validated UHPLC-MS/MS multiple reaction monitoring (MRM) method using deuterated internal standards. Oxidative stress and inflammation are suspected to play a major role in the pathogenesis of CRC [20, 21].

In blood we will evaluate the following:
Lipid profile change from baseline, including total cholesterol, low-density lipoprotein (LDL) cholesterol, high-density lipoprotein (HDL) cholesterol, and triglyceridesGlycemic profile change from baselineInflammatory profile change from baseline: high-sensitivity C-reactive protein (hs-CRP), circulating levels of inflammatory cytokines (interleukin-1ra [IL-1ra], interleukin-1 beta [IL-1β], IL-2, IL-4, IL-6, IL-8, IL-10, IL-12, IL-17, IL-18, tumor necrosis factor alpha [TNFα], interferon gamma [IFNγ], vascular endothelial growth factor [VEGF], monocyte chemoattractant protein-1 [MCP-1], and IFNγ-inducible protein 10 [IP-10]).

In urine we will analyze:
1,4-dihydroxynonane mercapturic acid (DHN-MA) change from baseline. This specific biomarker is the major urinary metabolite of HNE, a lipid peroxidation product [18].

### Sample size and power calculation

The sample size was determined to detect an anticipated change in fecal water-induced DNA damage evaluated through the comet assay of 25% from baseline, between the MBD and the PVD interventions. On the basis of a previously published trial conducted to test the efficacy of a dietary intervention on fecal water-induced DNA damage evaluated through the comet assay [14], a sample size of at least 50 in each group of the study will allow us to obtain a statistical power of 80% (beta) and alpha = 0.05, totaling 150 individuals. In case of loss to follow-up, extra volunteers will be enrolled to compensate. Losses will be included in the intention-to-treat but not in the per-protocol analyses.

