### Recruitment and randomization

Male and female participants will be recruited using advertisements on local media, newspapers, social media, official papers, and websites. We will also recruit from our existing database of participants and friends or relatives of the hospital and university staff. After approval and completion of the initial assessment, the subjects will be formally included in the study and randomized with a simple 1:1:1 randomization to the intervention arms through a web-based online randomization procedure. No adaptive randomization procedures will be performed. The random allocation sequence will be produced and managed by an investigator who will not take part in the participants’ recruitment. The order of assignments will be kept hidden from the investigators who will enroll participants or assign interventions. Group allocation will be presented on a folded paper in a sealed envelope.

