### Statistical analysis

Outcomes will be analyzed by intention-to-treat and on-treatment procedures. The primary outcome (fecal water genotoxicity) will be analyzed within each group using paired comparison *t* tests to evaluate whether the changes from baseline to 3 months will be statistically significant. The absolute change (mean value at baseline subtracted from the mean value after intervention for each subject) will be estimated with independent *t* sample tests. One-way analysis of variance will be used for testing differences between changes in the three diet groups. A general linear model for repeated measurements (after checking regression assumptions) will be performed in order to compare the effects of the three different treatments. A model with adjustments for multiple confounders will be used. Data for the general linear model will be reported as geometric means with their standard errors. Multiple strategies will be employed to reduce attrition, including an accurate recruitment, a structured and time-limited protocol, the inclusion of a run-in period, the limitation of the burden and inconvenience of data collection on the participants, and the development of a trusting and collaborative relationship between research units and participants. If a participant does not attend a scheduled appointment, a maximum of three telephone calls will be made and one email sent prior to withdrawing the participant from the study. If a participant wants to withdraw from the study intervention, the reason for withdrawal will be documented in the participant records for the subsequent analysis in the interpretation of the results.

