Before starting the data analysis, the level, pattern, and likely causes of the missingness in the baseline variables and outcomes will be investigated by forming appropriate tables. This information will be used to determine whether the level and type of missing data have the potential to introduce bias into the analysis results or substantially reduce the precision of estimates for the proposed statistical methods. Sensitivity analyses will be undertaken, based on the assumption that missing outcomes are the worst possible, or the best possible, in different randomization groups. If these analyses show that conclusions may differ based on missing values, then supplementary multiple imputation for missing values will be undertaken. These analyses will account for results of any losses to follow-up insofar as they pertain to differences in measured variables (i.e., under the assumption of missing at random). A *p* value < 0.05 will be considered statistically significant. Statistical analyses will be performed using SPSS software for Macintosh (SPSS Inc., Chicago, IL, USA).

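### The stated 80% power and 5% alpha cover MBD vs PVD only, and the analysis section does not name that comparison, or any other, as the test that decides the primary outcome

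*Protocol article*

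**What the plan says.** The section on sample size and power gives the target as a change in fecal water-induced DNA damage "evaluated through the comet assay of 25% from baseline, between the MBD and the PVD interventions". It states that 50 or more participants per arm "will allow us to obtain a statistical power of 80% (beta) and alpha = 0.05". (The label is a slip: 80% is the power, so beta is 20%.) No SD or baseline mean is given; the section refers only to an earlier dietary trial.

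The Statistical analysis section then names these analyses for the primary outcome or for comparing the diets:

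- a paired t test within each of the three arms;
- independent-sample t tests on absolute change, without saying which pair or pairs;
- an ANOVA: "One-way analysis of variance will be used for testing differences between changes in the three diet groups";
- a general linear model for repeated measurements comparing the three treatments, reported as geometric means;
- a model adjusted for confounders.

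Outcomes are to be analyzed both by intention-to-treat and on-treatment, and neither set is called primary. The threshold is not restricted to any one of these tests: a p "value < 0.05 will be considered statistically significant". On the third arm, the section on interventions and timeline describes MBD-T as "presumably medium risk", that is, between the other two diets.

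**The concern.** A power statement describes one test at one alpha. Here it describes MBD vs PVD, but the analysis section never says that this comparison decides the trial, or by which of the listed methods. Read as written, a positive conclusion could rest on any pair of arms, on the ANOVA, on a within-arm change or on either analysis set. The more of these that may count, the further the error rate rises above 5%. If the plan instead holds 5% by making the three-arm ANOVA the gate, or by dividing alpha, the powered comparison may no longer have 80%.

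The third arm adds a practical problem. If MBD-T does lie between the other diets, its contrasts concern a smaller difference than the one the trial was sized for. The protocol does not say that the 80% does not extend to them.

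**Working it through.** **Inputs.** From the documents: 50 per arm, three arms ("randomized with a simple 1:1:1 randomization to the intervention arms"), 80% power, alpha 0.05, and a 25% target for MBD vs PVD. Assumed: two-sided tests, normally distributed changes with equal SD, and the 25% read as a difference in change relative to baseline.

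**1. The plan's own figure.** Without an SD, the 50 per arm cannot be reproduced forwards. Solving backwards with the normal approximation:

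d = (z₀.₉₇₅ + z₀.₈₀) / √(n/2) = (1.960 + 0.842) / √25 = 0.560, so SD = 25 / 0.560 = 44.6% of baseline.

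With the noncentral t distribution (98 df), d = 0.566 and SD = 44.2%. The power results in steps 3 and 4 use d = 0.566.

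**2. Error rate if several tests may count.** This was simulated under no effect with three arms of 50 (200,000 trials).

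- Any of the three pairwise t tests at 0.05: 12.2%. Independent tests would give 1 − 0.95³ = 14.3%; the simulation allows for the shared arms.
- Any pairwise test, the ANOVA or a within-arm paired test, with no change in any arm: 18.7%.
- ANOVA alone, or a pairwise test read only after a significant ANOVA: 5.0%.

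These rates do not depend on the SD.

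**3. Power if the ANOVA decides.** The noncentrality is λ = 50 × Σ(μᵢ − μ̄)², referred to F with 2 and 147 df.

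- MBD-T midway, means 0, d/2, d: λ = 50 × d²/2 = 50 × 0.160 = 8.0; power 71%.
- MBD-T a quarter of the way from one arm: power 75%.
- MBD-T equal to another arm: λ = 50 × 2d²/3 = 50 × 0.213 = 10.7; power 83%.

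The chance that both the ANOVA and the MBD vs PVD t test are significant is 70% with MBD-T midway and 76% with MBD-T equal to another arm.

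**4. Power for other choices at the same effect.**

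- Bonferroni over three pairs (alpha 0.0167), MBD vs PVD: 65% by noncentral t, 66% by the normal approximation. Restoring 80% takes 67 per arm.
- One MBD-T contrast at 0.05 with MBD-T midway: the difference is d/2 = 0.283, the noncentrality is 0.283 × √25 = 1.41, and power is 29%.
- MBD vs PVD as the only confirmatory test: alpha 5% and power 80%, as stated.

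**5. Dependence on the missing SD** (normal approximation, 25% difference, 50 per arm):

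| SD of change, % of baseline | Power at 0.05 | Power at 0.0167 |
|---|---|---|
| 30 | 99% | 96% |
| 40 | 88% | 77% |
| 44.6 | 80% | 66% |
| 50 | 71% | 54% |
| 60 | 55% | 38% |

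With an SD of about 38.6% or less, 50 per arm keeps 80% even at alpha 0.0167.

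**The case against.** The strongest reply is that the protocol has one primary outcome and sizes the trial for one named contrast. If that contrast is the confirmatory test, 5% and 80% both stand and the other analyses are supportive. This is right. A reader might infer that one of the two figures must be untrue; the documents do not support that. They fail to say which test carries the figures, which is a weaker fault.

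Several narrower objections also stand. The text does not say that all three pairs will be tested. The 19% needs a within-arm change to count as success, and those tests ask a different question from whether the diets differ. Different models applied to the same contrast are strongly correlated and add error only if the best result may be chosen. The midway position of MBD-T is an assumption: the protocol's phrase concerns cancer risk, not the comet assay.

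A reader might also extend the point to the blood and stool outcomes, count pairwise tests across every cytokine and ask for false-discovery control. The documents do not state that pairwise testing or claim confirmatory status for those outcomes, and such adjustment is ordinary analysis-plan content. It is not part of this point.

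The reply that a full analysis plan may settle the testing order carries less weight. The protocol is not merely silent: it lists competing tests for the primary outcome and sets one unrestricted threshold over them.

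**Conclusion.** The point holds in a limited form. The stated alpha and power belong to MBD vs PVD, and the analysis section does not designate that comparison, a model or an analysis set as decisive.

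The error rate ranges from 5% (one named test, or the ANOVA as gate) to about 12% (any pairwise test) or about 19% (within-arm changes also counted). Power ranges from the stated 80% (MBD vs PVD alone) to about 71% for the ANOVA with MBD-T midway, and up to 83% if MBD-T equals another arm. An MBD-T contrast has about 29% if its effect is midway. All the power figures are conditional on the effect implied by taking 50 per arm and 80% as exact, and with a smaller or larger SD they move as tabulated. The error rates are free of that assumption but depend on what is allowed to count as success. Whether 80% is right for MBD vs PVD itself can be neither confirmed nor refuted from the article.

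**What to change.** In the Statistical analysis section, name the between-arm comparison of MBD vs PVD in change in the genotoxicity index as the sole primary test, at two-sided 0.05. Specify one model, with its scale and covariates, and the intention-to-treat set. The scale needs stating because the t tests and ANOVA use absolute change while the general linear model is to be reported as geometric means.

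Describe the ANOVA, the within-arm tests, the remaining models and the on-treatment set as supportive. Test the MBD-T contrasts only in a fixed, stated sequence after the primary test succeeds, or report them as estimates with confidence intervals.

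In the section on sample size and power, state that the 80% applies to MBD vs PVD only and that an MBD-T contrast has about 29% power if its effect is midway, under the implied SD. Correct the beta label at the same time.

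The cost is wording only, with no added participants. The downside is that the MBD-T contrasts lose stand-alone confirmatory status.
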